### Statistical methods

#### Randomization

For the phase III trial, randomization will be performed on an individual basis based on a 1:1 allocation ratio. Randomization will be stratified by investigational site, treatment line (first or second), and type of cancer (breast, colon, rectal or prostate cancer versus bladder, ovarian, or lung cancer or lymphoma). Because of the number of strata foreseen, randomization by minimization will be implemented [32].

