Goodwin [6]	Multicenter RCT	335	Older women (≥65y) newly (<2 months) diagnosed with breast cancer	≈72y	12-month nurse case management	Type and use of cancer-specific therapies received in the first 6 months after diagnosis. Patient satisfaction and arm function	- More appropriate management for women receiving nurse case management (Breast-conserving surgery, adjuvant radiation, radiation therapy, axillary dissection and breast reconstruction surgery). Better arm function and higher satisfaction in intervention group.
McCorkle [15]	Single centerRCT	375	Old patients (≥60y) newly diagnosed with solid cancer	60–92	4-week home-based case management by nurse	Length of survival	- Longer survival in intervention group than in usual care group (*p* = 0.001). Survival advantage for intervention group in late stage patients.
Galvao [8]	Two-arm single center RCT	57	Prostate cancer patient without bone metastases treated by AST (≥2 months)	≈70y	12-week progressive resistance and aerobic training (2/week) by an exercise physiologist	Muscle mass, strength, physical function, QoL	- Significant change in total body lean mass, muscle strength and endurance (*p* < 0.05). Change in QoL for general health (*p* = 0.022), vitality (*p* = 0.019) and physical health composite score (*p* = 0.02).

**QoL* quality of Life, *RCT* randomized controlled trial

Geriatric intervention has also been shown to increase overall survival (OS) in the general elderly population in randomized controlled trials (RCTs) [11, 12]. However, only few RCTs have investigated the impact specifically for elderly cancer patients, with conflicting results. Bourdel-Marchasson et al. [13] found no impact on 1-year mortality after a nutritional intervention, and in a sub-analysis of a larger trial, Rao et al. [14] found no difference in 1-year survival after geriatric case-management for elderly cancer patients. An improvement in survival was reported in an RCT involving case-management in the form of a one-month nurse intervention for post-surgical elderly cancer patients, including 375 patients older than 60 years, but this benefit was restricted to the sub-population of patients with advanced disease [15].

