### Eligibility criteria

This study will include patients 70 years and older. In addition, patients must meet the following criteria: performance status 0 to 3 (WHO), candidate to 1^st^ line medical treatment (excluding best supportive care) of breast, colon, rectal, lung, prostate, bladder, or ovarian cancer and lymphomas (indolent and aggressive); excluding exclusive hormonotherapy (except prostate cancer); or, second line medical treatment (excluding Best Supportive Care) of breast, colon, rectal, prostate cancer, ovary and indolent lymphoma.

Exclusion criteria are life expectancy under 6 months, presence of any psychological, familial, sociological or geographical condition potentially hampering compliance with the study protocol and follow-up schedule, participation at the same time in another study in which investigational drugs are used, and patients who have already received two lines of treatment or for whom hormonal treatment (except for abiraterone acetate and enzalutamide in prostate cancer) or best supportive care is indicated.

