### Description of the interventions

All patients included in the randomized trial will receive cancer care according to ongoing standards in oncology. The content of this intervention has been precisely defined in a *cancer care protocol* by a panel of experts in geriatric oncology, and depending on the disease and stage. For patients specifically randomized in the “Case-management intervention”, intervention will, in addition, involve multidimensional geriatric assessments and case-management geriatric interventions tailored for the patient. Similarly, this specific geriatric intervention has been precisely defined in a *geriatric care protocol* by a panel of experts in geriatric oncology. We first describe the development process for the *cancer care protocol* and the *geriatric care protocol* followed by details of the content of each protocol.

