#### Sample size

Sample size was estimated for the randomized trial. For the null hypothesis we assumed no difference in OS and no difference in the three targeted HRQoL dimensions between the two intervention arms. Alternative hypotheses were two-fold: improvement in OS or improvement in HRQoL. The 5% two-sided type-1 error rate was therefore split between the two alternative hypotheses with 2% for OS and 1% for each of the three HRQoL dimensions. Sample size improvement for testing improvement in OS assumed the following hypotheses: 2% (two-sided) type-1 error rate, 85% power, anticipated 1-year 50% OS rate in the ‘usual care’ group [13], 60% expected 1-year 60% OS rate in the “Case-management” arm (ie anticipated hazard ratio, HR = 0.74). These hypotheses led to an estimated sample size of 1096 subjects (548 per group; 486 events) needed to detect a difference in OS (log-rank test). Sample size for testing improvement in HRQoL was based on a 3% (two-sided) type-1 error. If the intervention is effective, we expect that it will allow us to detect, at one year, a mean difference of 10 points or more for at least one of the three targeted HRQoL scores (common standard deviation of 20 points). Each of the three scales will be independently tested. Five hundred and forty eight subjects per group (as needed for OS comparison) will provide sufficient power (>90%) for independently testing the three HRQoL scales at 1% (2-group t-tests of equal means – common variance).

To anticipate for non-assessable subjects (10%), 1200 patients need to be randomized (ie with G8 score ≤ 14). Based on previous research [5] about 80% of the patients are expected to have positive G8, thus 1500 patients need to be screened for inclusion in the randomized trial.

Since 20% are expected to have normal G8 score, about 300 patients will be included in the parallel cohort. Following our previous experience with the ONCODAGE validation study [3] which included 1668 patients over 18 months, we expect that 800 patients will be screened each year, leading to an expected inclusion period of 1.5 to 2 years. To reach all endpoints, three years of follow-up are required, giving total study duration of 5 years.

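### The primary OS test leaves out disease extent, which forgoes some power but causes no bias

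*Protocol article*

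**What the plan says.** Under Randomization, the protocol article lists three minimisation factors: investigational site, treatment line, and "type of cancer (breast, colon, rectal or prostate cancer versus bladder, ovarian, or lung cancer or lymphoma". Statistical analyses makes the primary OS comparison a log-rank test stratified on the randomization factors at a 2% type I error. A variable left out of the allocation is therefore also left out of the primary OS test.

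Eligibility criteria admit "breast, colon, rectal, lung, prostate, bladder, or ovarian cancer and lymphomas (indolent and aggressive" and state no stage limit. Description of the interventions says that cancer care is defined "depending on the disease and stage". Baseline assessment, described for the usual-care arm and shared by both arms, includes disease history and tumor assessment.

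On survival after case management, the Background says of one cited cancer trial that "this benefit was restricted to the sub-population of patients with advanced disease".

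Sample size plans OS on "2% (two-sided) type-1 error rate, 85% power", an "anticipated 1-year 50% OS rate in the" usual-care group, 60% with case management ("ie anticipated hazard ratio, HR = 0.74"), and arrives at "1096 subjects (548 per group; 486 events".

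**The concern.** Disease extent is commonly among the stronger predictors of one-year survival in a mixed cancer population. The two cancer groups are a weak substitute for it. One holds indolent lymphoma together with lung cancer. The other pools breast, colorectal and prostate cancer with no split by extent.

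When a strong prognostic factor is left out of a log-rank test, the marginal hazard ratio moves towards 1 and the test loses power against a given within-group effect. OS is one of the co-primary endpoints and is planned at 85% power, so a few points are worth having if they cost little.

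**Working it through.** **1. The plan's own figure.** Inputs, all from Sample size: two-sided alpha 0.02, power 0.85, one-year OS 50% versus 60%.

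- HR = ln 0.6 / ln 0.5 = 0.737, printed as 0.74.
- Events (Schoenfeld) = 4(2.326 + 1.036)² / (ln 0.737)² = 486, as stated.
- Mean one-year event probability = (0.50 + 0.40)/2 = 0.45, so N = 486/0.45 = 1080. Freedman's formula gives 494 events and N = 1098. Both are within 3% of 1096.

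There is no arithmetic error here.

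**2. Type I error.** Simulated null trials (N = 1096, 3000 per setting; assumed advanced share 30–70%, assumed hazard ratio for extent 2 or 4) reject in 1.6% to 2.4%, with or without extent. The nominal rate is 2%, with Monte Carlo standard error √(0.02 × 0.98/3000) = 0.26 points. Nothing is inflated.

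**3. Chance imbalance.** With 600 per arm and half the patients advanced, the SD of the difference in share is √(2 × 0.5 × 0.5/600) = 2.9 points, with a 95% range of ±5.7. If control OS is 30% and 70% in the two groups, a 5.7-point imbalance moves one-year OS by 0.057 × 40 = 2.3 points, against a 10-point target.

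**4. Power with a common HR of 0.737 within each group.** N = 1080, half in each group (assumed), exponential survival, censoring at one year, 2000 runs. The proxy column uses a stratum that agrees with extent in 70% of patients, to mimic what line or cancer type might capture.

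| Control one-year OS by extent | Without extent | 70% proxy | With extent |
|---|---|---|---|
| 40/60% | 84% | 84% | 85–86% |
| 30/70% | 78% | 79% | 85–86% |

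The loss is about 2 points in the first row and 7 to 8 in the second. These rows correspond to hazard ratios for extent of ln 0.4/ln 0.6 = 1.8 and ln 0.3/ln 0.7 = 3.4. The step 2 simulation design, run with the same treatment effect, gives losses of 2 to 3 points at a ratio of 2 and 6 to 13 points at a ratio of 4.

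**5. Power with the protocol's overall 50% versus 60% held.** Step 4 fixes the HR within groups, so overall treated OS falls slightly short of 60%: 0.5(0.4^0.737 + 0.6^0.737) = 59.8%, and 59.0% at 30/70. If the overall difference is held at 10 points, the log-rank test without extent has 85% and 86% power, and with extent 87% and 92%.

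**6. How to include extent.** The number of sites is not given; 30 are assumed. Site × line × type makes 30 × 2 × 2 = 120 strata, or 1080/120 = 9 patients each. Crossing with extent makes 240 strata of 4.5. At 40/60 this takes power from about 81% to about 75%, and at 30/70 it changes little. Stratifying on line, type and extent (8 strata of 135) gives about 84–86%. The absolute levels with site depend on the assumed site sizes and on how well allocation balances within cells. A repeat without balance within cells put both site-crossed figures lower but showed the same pattern.

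**The case against.** The strongest reply is step 5: on the overall difference that the protocol states, the planned power is not lost. That stands, and it makes the proposal an efficiency gain and not a repair.

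Second, the planned test is stratified on line and cancer type, which may carry part of the information on extent. This stands only in part: a 70% proxy recovers about 1 of the 8 points at 30/70.

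Third, covariate lists and subgroup analyses belong in the SAP, which is not shown, and the article already foresees Cox modelling for OS and further covariates in the HRQoL variance analysis. Their lack of detail is indeed no finding. The strata of the primary OS test, however, are fixed in the article.

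Fourth, the mix of stages is inferred. A 50% one-year survival, second-line eligibility and an objective-response endpoint could point to a mostly advanced population, in which extent would discriminate less. That stands as a limit on the size.

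A reader might also infer more than the documents support:

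- *That a one-year difference would be hard to attribute to case management.* Randomization protects against this, and step 3 shows that the likely imbalance is small.
- *That a stage-specific benefit motivates the trial.* The Background and Discussion rest on limited and conflicting evidence overall. The stage finding comes from one 375-patient trial, whose Table 1 row also reports longer survival in the intervention group as a whole.
- *That the loss could exceed 20 points.* A 20/80% split gives 65% versus 86%, but it implies a control median of 12 × ln 0.5/ln 0.2 = 5.2 months in half the patients, in a trial that excludes life expectancy under 6 months.

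**Conclusion.** The point holds as one of efficiency. The primary OS test is tied to site, line and a coarse two-level cancer type, so disease extent is left out although it can be derived from baseline data. There is no bias, no type I error inflation and no error in the sample size.

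The cost is about 2 to 8 points of OS power if control one-year OS differs by extent from 40/60% to 30/70%, with an assumed equal mix and a common HR of 0.737 within groups. It is smaller if extent predicts little or if the population is mostly advanced. If the overall 50% versus 60% holds, the planned power is kept and adjustment adds to it.

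Adjustment would not rescue the trial if the benefit existed only in advanced disease. With 30% to 70% of patients advanced, the simulated power is 11–63% without extent and 15–74% with it. A treatment-by-extent estimate can inform that question but cannot settle it.

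**What to change.** Define extent from data recorded before randomization: localized or locally advanced versus metastatic, and for lymphoma indolent versus aggressive. Pre-specify it in the primary OS comparison at the 2% level in one of two ways: a Cox-model test adjusted for extent, line and cancer type, or a log-rank test stratified on line, cancer type and extent. Do not cross extent with every site, because the sparse strata lose the gain. The site-stratified log-rank can be kept as a sensitivity analysis.

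Add extent to the adjusted HRQoL variance analysis, and report one treatment-by-extent estimate labelled exploratory. Adding extent to the minimisation is optional, and only if accrual has not begun. It would need one more field on the randomization form and could loosen balance on the other factors slightly.

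The cost is a definition, a few sentences in the analysis plan, slightly more analysis work, and a departure from stratifying the primary OS test on site. The sample size does not change.

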#### Sample size

Sample size was estimated for the randomized trial. For the null hypothesis we assumed no difference in OS and no difference in the three targeted HRQoL dimensions between the two intervention arms. Alternative hypotheses were two-fold: improvement in OS or improvement in HRQoL. The 5% two-sided type-1 error rate was therefore split between the two alternative hypotheses with 2% for OS and 1% for each of the three HRQoL dimensions. Sample size improvement for testing improvement in OS assumed the following hypotheses: 2% (two-sided) type-1 error rate, 85% power, anticipated 1-year 50% OS rate in the ‘usual care’ group [13], 60% expected 1-year 60% OS rate in the “Case-management” arm (ie anticipated hazard ratio, HR = 0.74). These hypotheses led to an estimated sample size of 1096 subjects (548 per group; 486 events) needed to detect a difference in OS (log-rank test). Sample size for testing improvement in HRQoL was based on a 3% (two-sided) type-1 error. If the intervention is effective, we expect that it will allow us to detect, at one year, a mean difference of 10 points or more for at least one of the three targeted HRQoL scores (common standard deviation of 20 points). Each of the three scales will be independently tested. Five hundred and forty eight subjects per group (as needed for OS comparison) will provide sufficient power (>90%) for independently testing the three HRQoL scales at 1% (2-group t-tests of equal means – common variance).

To anticipate for non-assessable subjects (10%), 1200 patients need to be randomized (ie with G8 score ≤ 14). Based on previous research [5] about 80% of the patients are expected to have positive G8, thus 1500 patients need to be screened for inclusion in the randomized trial.

Since 20% are expected to have normal G8 score, about 300 patients will be included in the parallel cohort. Following our previous experience with the ONCODAGE validation study [3] which included 1668 patients over 18 months, we expect that 800 patients will be screened each year, leading to an expected inclusion period of 1.5 to 2 years. To reach all endpoints, three years of follow-up are required, giving total study duration of 5 years.

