#### Statistical analyses

For the randomized trial, different analysis sets will be defined including the intent-to-treat (ITT) population (all randomized patients included and analyzed according to the allocated intervention), modified ITT population (mITT: all randomized patients with baseline HRQoL included and analyzed according to the allocated intervention) and per protocol population (PP: eligible patients and analyzed according to the intervention actually received). These three populations will be described according to the following characteristics: compliance with eligibility criteria, epidemiological characteristics, clinical and laboratory characteristics, treatment characteristics, and HRQoL. For the co-primary endpoints, the primary analysis will be conducted in the mITT population, with sensitivity analyses conducted in the PP population. OS will first be compared based on a log-rant test stratified on randomization factors (2% type 1 error rate). Additional analyses will be conducted including Cox regression modeling to provide an estimate of the effect size of the intervention, after checking for underlying model assumptions. For each targeted HRQoL dimension, a *t*-test assuming common variances will be conducted (1% type 1 error rate). Sensitivity analyses assuming a mean difference of 5 points or more for at least one of the targeted HRQoL scores will be conducted. In addition, variance analysis will be conducted for adjustment on randomization factors and additional covariates. Other endpoints will be analyzed using standard statistical techniques. PFS will be analyzed using the same methods as for OS. Censoring mechanisms for the analysis of TUDD will follow recommendations from Bonnetain et al. [28]. With regards to HRQoL data, missing data analysis will be performed to determine the missing data profile. Longitudinal models will be fitted to provide a description of the HRQoL over time and investigate effect of the intervention. For patients treated in the “Case-Management” arm, the analysis of geriatric parameters will involve summary statistics presented at various time-points as well longitudinal analysis to investigate trends over time.

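### The fixed 2/1/1/1 split is valid but discards the alpha of every rejected hypothesis; weighted Holm would raise OS power from 85% to about 87% after one HRQoL win, at no cost

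*Protocol article*

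**What the plan says.** Protocol article, Sample size: "The 5% two-sided type-1 error rate was therefore split between the two alternative hypotheses". The shares are then given as "with 2% for OS and 1% for each of the three HRQoL dimensions". The article adds that the three scales are tested independently of one another. The OS test is sized at "2% (two-sided) type-1 error rate, 85% power", for one-year OS of 50% against 60% ("ie anticipated hazard ratio, HR = 0.74"), which leads to 486 events and 548 patients per group.

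Statistical analyses carries the same levels into the analysis. The log-rank test is "stratified on randomization factors (2% type 1 error rate") and the t-test for each scale is described as "assuming common variances will be conducted (1% type 1 error rate"). OS is to be compared first, but that sets an order only and changes no level. Neither section says that alpha moves to another hypothesis after a rejection.

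The primary objective counts the trial as positive if OS or at least one targeted scale improves. Evaluation criteria is more detailed: an OS improvement is subject to a condition on HRQoL deterioration, and an HRQoL improvement is subject to a condition that OS does not differ significantly.

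**The concern.** Once a hypothesis has been rejected, its share of the 5% is no longer needed to protect the others. Under the stated rule, a win on one scale leaves OS at 2% although 4% of alpha would cover the three hypotheses still open and the full 5% may be used for them. The rule spends less than it is allowed to.

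What is at stake is the second and later claims. Evaluation criteria judges OS and HRQoL separately, and the Discussion presents the joint view of life span and HRQoL as the merit of the design. Whether the trial can claim a survival benefit in addition to an HRQoL benefit is therefore a reported conclusion, and that is where the power is lost.

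**Working it through.** **Inputs.** From Sample size: alpha 2% for OS and 1% for each scale; one-year OS 50% and 60%; 486 events; 548 per group; HRQoL difference 10 points, SD 20. From Randomization: 1:1 allocation.

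**1. Reproduce the plan's figure.**
- HR = ln 0.6 / ln 0.5 = 0.737, so |ln HR| = 0.3052.
- Schoenfeld events = 4 × (2.326 + 1.036)² / 0.3052² = 485.6, that is 486. This matches the article.
- The four levels sum to 2% + 1% + 1% + 1% = 5%.

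**2. Levels under weighted Holm with weights 2:1:1:1.** Each open hypothesis is tested at 5% × its weight / sum of the open weights.
- OS with no scale won: 5% × 2/5 = 2%.
- OS after one scale: 5% × 2/4 = 2.5%.
- OS after two: 5% × 2/3 = 3.33%.
- OS after all three: 5%.
- Each scale after OS: 5% × 1/3 = 1.67%.

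The first step uses the article's own levels and later levels only rise, so nothing that is now rejected is lost. Error control holds for any correlation between endpoints: when the first true null is rejected, all true nulls are still open, so its level is at most 5% × its weight / sum of the true-null weights, and these levels add up to at most 5%.

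**3. OS power with 486 deaths.** Power = Φ(√486 / 2 × 0.3052 − z) = Φ(3.364 − z).

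| Scales won | OS level | z | OS power |
|---|---|---|---|
| none | 2% | 2.326 | 85.0% |
| one | 2.5% | 2.241 | 86.9% |
| two | 3.33% | 2.128 | 89.2% |
| three | 5% | 1.960 | 92.0% |

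With HR rounded to 0.74, or with Freedman's formula, the absolute powers are up to about 2 points lower. The gain stays at about 2 points after one win and 7 to 7.6 points after three.

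**4. Simulation of the whole procedure** (assumed: correlation 0.5 between scales, OS independent of HRQoL). With a true 10-point effect, OS power under weighted Holm is 87.0% if one scale improves, 89.1% if two do and 92.0% if all three do. With no HRQoL effect it is 85%. Under the global null the overall error is 4.7% for both rules. With all three scales truly improved and no OS effect, the OS error is about 5.0%. In every scenario the chance of at least one rejection is the same under both rules.

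**5. HRQoL power at 1%.** With 548 per group, SE = 20 × √(2/548) = 1.21 and 10 / 1.21 − 2.576 = 5.7, so power is about 100%. With an assumed 300 assessable per group, SE = 1.63 and power is still 99.98%. At the planned effect, passing alpha to the scales gains almost nothing.

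**The case against.** **The split is valid and consistently stated.** This stands. A reader might infer that the multiplicity plan is wrong. It is not: the levels sum to 5% and both sections agree. An analysis plan that is not shown could also add recycling. Against that, the article does state the analysis levels, as 2% and 1% without qualification, so the point rests on its text.

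**The primary decision gains nothing.** This also stands. The objective asks for OS or at least one scale, and the first rejection is made at the same levels under both rules.

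**The size is easily overstated.** A reader might set 85% against 92% as the price of the split. The 92% needs all three scales to be rejected first, whereas the article plans on a difference in at least one scale, which gives about 87%. Larger gains for the scales can be shown: with a true 5 points on every scale and 300 assessable per group, power per scale goes from about 69% to 81%. But the article plans on 10 points and names 5 only for a sensitivity analysis.

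**The thresholds in Evaluation criteria may bind before alpha does.** That section calls a one-year OS difference of at least 10% and an HRQoL difference of at least 10 points significant. If these are required of the observed results, alpha hardly matters. With 548 per group and a mean OS of 55%, SE = √(2 × 0.55 × 0.45 / 548) = 3.0 points, so an observed 10 points gives z = 3.3 and p of about 0.001. The differences needed are only about 7.0 points at 2% and 5.9 at 5%. The gain then nearly vanishes. The text can also be read as stating design targets, in which case the table stands.

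**Recycling touches the conditions in Evaluation criteria.** This is correct. If OS moves to 2.5% to 5% after HRQoL wins, it becomes unclear at which level an OS difference counts as significant for the condition attached to an HRQoL win. An adverse OS result with p = 0.03 would pass at 2% and fail at 5%. The remedy has to settle this.

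**Conclusion.** The point holds as a free, optional gain in efficiency. The stated rule is valid but is dominated by a step-down rule with the same starting levels and the same family-wise error. The gain in OS power is about 2 points if one scale is won, about 4 if two are and at most 7 if all three are; it is nil without an HRQoL win. For scale, 86.9% power at a fixed 2% would take 4 × (2.326 + 1.123)² / 0.3052² = about 511 deaths, 25 more than planned.

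The documents do not support saying that the error rate is uncontrolled, that the trial is less likely to succeed on its primary objective, or that 92% is what the plan generally forgoes.

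The power at each level rests on proportional hazards, 486 deaths and the planned hazard ratio. The simulated figures also rest on the assumed correlations; error control does not. All of it presumes that the 10% and 10-point thresholds are not additional requirements on the observed differences.

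**What to change.** - **Sample size and Statistical analyses:** keep the starting levels and add that, when a hypothesis is rejected in favour of case management, its alpha passes to the remaining hypotheses in proportion to their weights. List the levels: OS at 2.5%, 3.33% and 5% after one, two and three scales; each scale at 1.67% after OS.
- **Evaluation criteria:** name a fixed level for the condition on HRQoL deterioration and for the condition on an OS difference, and say that passed-on alpha does not alter it.
- **Timing:** settle both before unblinding; a rule added later would not be credible.

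The cost is about a paragraph of text and one further sentence. No patients, visits or data are added, and no claim now available is lost.
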